## Methods

### Study Design Summary

The core design is a randomized, two-arm, parallel, multi-site clinical trial. Inclusion/exclusion criteria were chosen to enroll a population with chronic mental illness who are overweight or obese and who may safely participate in a weight loss intervention including moderate intensity exercise. Interested mental health consumers are being screened for eligibility at 10 psychiatric rehabilitation centers across Maryland. Three hundred and twenty adult participants completing screening are targeted for enrollment and randomization to the ACHIEVE (Achieving Healthy Lifestyles in Psychiatric Rehabilitation) intervention or usual care. Intervention participants receive group and individual weight management sessions and group physical activity classes. In the initial 6-month intervention phase, study interventionists lead the sessions and also train designated rehabilitation program staff. A 12-month maintenance intervention phase follows in which interventionists continue leading some sessions and trained rehabilitation staff assume responsibility for delivering part of the intervention. Interventionists also provide education to rehabilitation program kitchen staff to increase options for healthy meals served on-site. Follow-up data collection occurs at 6, 12, and 18 months from baseline. The study was approved by the Johns Hopkins Institutional Review Board (protocol number NA00015231).

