### Study sites and population

The study sites will include 10 community psychiatric rehabilitation programs across urban and suburban Maryland. Each location shares certain features: (1) adult psychiatric rehabilitation day program with consumers attending regularly at least 3 days a week; (2) space for on-site physical activity classes; and (3) meals served to consumers. The trial is enrolling men and women, age 18 and older who are overweight (body mass index ≥ 25.0 kg/m^2^) or obese and attend the psychiatric rehabilitation programs. By definition of their psychiatric rehabilitation attendance, these participants have a serious mental illness diagnosis. Persons with serious mental illness that receive care from rehabilitation programs' on-site mental health clinics are also eligible for recruitment. The inclusion and exclusion criteria for the trial are listed below.

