### Randomization and Blinding

After baseline data collection and before the intervention begins, participants meet with study staff and the intervention arms of the study are described in detail. The study coordinator confirms that the participant meets eligibility criteria, and that all required baseline data have been collected. Participants interested in enrollment are consented individually and randomized to either the intervention or the control group. The study coordinator ascertains and communicates treatment assignments to participants [31]. Randomization is stratified by gender and site using blocks of sizes 2 and 4 in random order to create the randomization sequence for each stratum.

Due to the nature of the intervention, both participants and interventionists will be aware of the assignment. The following mechanisms are in place for data collection staff to be masked to treatment assignment: 1) designating and tracking unmasked study staff; 2) excluding data collection staff from any part of intervention delivery; 3) performing outcome assessments in separate rooms than the intervention; and 4) reminding participants not to share their group assignment. Until the trial end, investigators, staff and participants are masked to outcome data with the exception of the trial statistician and data analyst. In addition, the primary outcome variable, weight, is subject to very little measurement bias [32].

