### Data Analysis

Randomly assigned intervention group (i.e., behavioral intervention or control) is the main independent variable for intent-to-treat analysis [47]. The co-primary outcomes are weight loss at 6 and 18 months. To evaluate the efficacy of the intervention for each of these outcomes, generalized estimating equations are used [48]. These models account for the longitudinal nature of the trial and incorporate baseline, and 6, 12 and 18-month measurements and will account for study site and other baseline characteristics found not to be balanced by randomization. For secondary outcomes that are categorical, logistic regression GEE models are used according to the same principles outlined above for continuous outcomes.

In addition to the analyses that preserve the intention to treat principle, analyses on subgroups defined post-randomization are exploratory. These include analyses in participants who attended the majority of weight management and exercise intervention sessions.

Although second generation antipsychotics and other psychotropic medications can induce substantial weight gain [3,9], we expect that both study groups will be equivalent in their distribution of these medication due to the process of randomization. Several analytical approaches are planned to address three main potential effects of antipsychotic and other concomitant medication on study outcomes; these include: (1) imbalances in medication use between the intervention and control groups, despite randomization procedures, (2) variation in intervention efficacy by medication or medication class, and (3) changes in drug use after randomization.

The analytic approach to handle missing data will be anchored on the assumption that data is missing at random (MAR), where the probability of missing can depend on all observed information such as measured weights and covariates but does not depend on variables that are not recorded. The analysis model will include parameters for visit specific means for each treatment group, baseline covariates associated with study retention, and use an unstructured covariance structure. Missing at random is almost never strictly correct, but careful modeling should make the missing data process as close to MAR as possible. Primary analyses will be conducted under the assumption of MAR; sensitivity analyses will be based on sensible "missing not at random" scenarios to evaluate the robustness of the inferences under the MAR assumption.

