## Discussion

Despite successful behavioral weight loss interventions in the general population, few randomized controlled trials of comprehensive behavioral weight loss interventions among persons with serious mental illness have been performed [51]. Given the high prevalence of obesity and cardiovascular risk factors, effective weight loss programs are needed in this vulnerable population. The ACHIEVE investigators led a previous pilot weight loss study (n = 52) in two psychiatric rehabilitation programs and demonstrated preliminary success with high levels of recruitment, retention and pre/post weight loss of 4.8 pounds [52]. The ACHIEVE Trial will definitively test the effectiveness of this innovative, practical intervention to realize and sustain weight loss in overweight and obese persons with serious mental illness. If successful, the intervention will be a model program that should provide important health benefits by reducing cardiovascular disease risk for persons with serious mental illness, and with appropriate resources, could be disseminated widely.

This study compares the effectiveness of a multifaceted weight loss intervention to a standard care group among persons who often have cognitive impairments and other comorbidities. Behavioral weight loss trials have shown efficacy for weight loss in other populations. For example, the ACHIEVE intervention was modeled after the PREMIER Trial, a comprehensive lifestyle intervention that incorporated education and counseling for diet and physical activity; the trial was proven effective for weight loss in the general population [39]. The Trial of Nonpharmacologic Intervention in the Elderly (TONE) study demonstrated significant weight loss (3.5-4.5 kg average reduction) among adults age 60-80 years over a 30-month follow-up period [53]. Similarly, initial 1-year results from the Look AHEAD (Action for Health in Diabetes) trial have shown that older adults (> 65 years) attend more lifestyle intervention sessions and participate in more physical activity than their younger counterparts [54]. At the end of a 6-month follow-up period, participants in The Weight Loss Maintenance trial demonstrated significant weight loss across racial and gender groups; weight loss was greatest among non-African American men and least among African American women [55].

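### Gender is a stratification factor but is not named in the primary model, and the rule for choosing covariates by observed imbalance would not be expected to add it

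*Protocol article*

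**What the plan says.** Under Randomization and Blinding, the article states: "Randomization is stratified by gender and site using blocks of sizes 2 and 4 in random order". There are therefore two stratification factors.

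Under Data Analysis, it states: "The co-primary outcomes are weight loss at 6 and 18 months". These are analysed with generalized estimating equations that use the baseline, 6-, 12- and 18-month measurements. On covariates, the models "will account for study site and other baseline characteristics found not to be balanced by randomization". The missing-data paragraph of the same section says that the analysis model will also include "baseline covariates associated with study retention, and use an unstructured covariance structure".

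Site is thus named as a covariate. Gender is not named as one anywhere in the section. Everything else is to be found by one of two criteria: imbalance after randomization, or association with retention.

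**The concern.** Two things are wrong with the stated rule.

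First, it omits one of the two factors by which the trial randomizes. Stratified blocking balances gender between the arms, which makes the treatment difference less variable to the extent that gender predicts weight change. A model without gender does not credit that gain. Its standard error is somewhat too large, its intervals somewhat too wide, and its test somewhat below the nominal level. A rule that adjusts for what turns out unbalanced cannot be relied on to repair this, because balance in gender is what the design produces.

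Second, observed imbalance is a poor criterion for any covariate. After proper randomization an imbalance is due to chance. What adjustment gains is set by the covariate's relation to the outcome. The rule can admit a covariate that is unbalanced but irrelevant, and pass over one that is balanced but strongly prognostic.

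At stake are some precision in the co-primary comparison and an analysis that matches the randomization.

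**Working it through.** **Inputs from the article.** 320 randomized (Study Design Summary); 10 sites (Study sites and population); stratification by gender and site in blocks of 2 and 4 (Randomization and Blinding); difference 4.5 lb, SD of change 12 lb, 80% follow-up, two-sided 0.05, power about 86% (Sample size and power). Equal allocation is assumed: it is not stated in words but fits the block sizes.

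**Step 1: the plan's own power.** Analysed per arm: 320 × 0.80 / 2 = 128. SE = 12 × √(2/128) = 1.5 lb. Effect/SE = 4.5/1.5 = 3. Power = Φ(3 − 1.96) = Φ(1.04) = 85.1% (84.8% with the noncentral t). The article obtains about 86% from a simulation whose full inputs are not shown. The figures agree to about a point, and the stated power is not in dispute.

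**Step 2: would the rule pick up gender?** An incomplete final block can leave an arm at most two ahead in any stratum. In 1,500 simulated allocations over 10 sites × gender with these block sizes, gender never differed between arms at p < 0.10 among all randomized. That threshold is an assumption, since the article gives none. Dropout could leave slight imbalance among those followed up.

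**Step 3: cost of omitting gender.** Let R² be the share of the variance of weight change that gender explains. With gender balanced, the true variance of the difference is 1.5² × (1 − R²) = 2.25(1 − R²), while the model without gender reports 2.25. Then:

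- type I error without gender = 2[1 − Φ(1.96/√(1 − R²))]
- power without gender = Φ((3 − 1.96)/√(1 − R²))
- power with gender = Φ(3/√(1 − R²) − 1.96)

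At R² = 0.05, √0.95 = 0.9747. Type I error: 1.96/0.9747 = 2.011, giving 4.43%. Power without gender: 1.04/0.9747 = 1.067, giving 85.70%. Power with gender: 3/0.9747 − 1.96 = 1.118, giving 86.82%.

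| Assumed R² | Type I error without gender | Power without | Power with | Points lost |
|---|---|---|---|---|
| 1% | 4.89% | 85.21% | 85.43% | 0.22 |
| 2% | 4.77% | 85.33% | 85.78% | 0.45 |
| 5% | 4.43% | 85.70% | 86.82% | 1.12 |
| 10% | 3.88% | 86.35% | 88.54% | 2.19 |

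**Step 4: selecting covariates by imbalance.** The simulation used stratified blocks over 10 sites × gender, 256 analysed, ten further baseline covariates, and a linear model with site. Covariates unbalanced at p < 0.10 were added, and this was compared with site, gender and all ten covariates fixed in advance. There were 8,000 replicates for type I error (Monte Carlo SE √(0.05 × 0.95/8000) = 0.24 points) and 2,000 for power (SE about √(0.86 × 0.14/2000) = 0.8 points).

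| Gender share | Share of each covariate | Type I error: by imbalance | Type I error: fixed set | Power: by imbalance | Power: fixed set |
|---|---|---|---|---|---|
| 2% | 1% | 4.30% | 4.92% | 85.25% | 87.80% |
| 2% | 3% | 3.89% | 5.03% | 85.90% | 94.40% |
| 5% | 1% | 4.14% | 4.90% | 85.20% | 88.55% |
| 5% | 3% | 3.50% | 5.34% | 86.90% | 94.45% |

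The imbalance rule is conservative for the same reason as in Step 3. A covariate that is not selected is nearly balanced, so the true spread of the estimate is smaller than the model reports. The power gap reflects ten covariates assumed to explain 10% to 30% of the variance together. It illustrates the mechanism and does not forecast this trial.

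**The case against.** The strongest reply is that little harm follows. Both departures are conservative, the loss from omitting gender is about two points of power at most over the range shown, and the article documents no variance share for gender. That stands, and it limits the weight of the point.

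The next reply is that an article leaves covariate lists to the full protocol or analysis plan. This stands for the imbalance threshold and for the names of the retention covariates, whose absence is not criticised here. It does not cover the rule itself, which the article states and which is a poor one. Naming site first does not expressly exclude gender, but nothing brings gender in.

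It is also fair that baseline weight is already in the longitudinal model, that separate approaches are planned for medication imbalance, and that covariates associated with retention are ordinary support for a missing-at-random analysis.

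Three stronger readings are tempting, and the article supports none of them:

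- **That the rule inflates type I error.** As written it does not. Selection on imbalance uses baseline data and allocation, not outcomes. Inflation appears only if someone fits several models and keeps the most favourable. With five candidate models in the simulation above, that gave 6.7% to 8.2%, but the article plans no such search and the figure depends on how many models are tried.
- **That an unmasked analyst will choose the model.** Randomization and Blinding exempts the trial statistician and data analyst from masking to outcome data. It does not say that they choose covariates, or that they do so after seeing outcomes.
- **That the article shows gender to be prognostic here.** The Discussion reports of another trial, at six months, that "weight loss was greatest among non-African American men and least among African American women". Those are race-by-gender groups in a different population. The sentence gives no gender main effect and nothing at 18 months.

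**Conclusion.** The point holds as a mismatch between design and analysis together with a badly chosen selection rule. It is certain on the text and modest in size. Omitting gender makes the test slightly conservative and costs up to about two points of power, on the assumptions that gender explains 1% to 10% of the variance of weight change and stays balanced among those analysed. Choosing covariates by imbalance also errs conservatively, under assumed covariate numbers, strengths and threshold. Validity of the co-primary tests is not threatened by the rules as written. What is lost is precision that the trial could have at no cost.

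**What to change.** In Data Analysis, name gender together with site as fixed covariates in the primary models; baseline weight is already there through the longitudinal model. Replace the clause on characteristics found unbalanced with covariates fixed in advance on prognostic grounds. Which covariates these are, beyond the two stratification factors, is for the trial team to decide. Keep the retention covariates that support the missing-at-random assumption. Any adjustment prompted by observed imbalance becomes a labelled sensitivity analysis.

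The cost is a change of wording before analysis. Table 1 shows that gender is collected at baseline, so naming it needs no new data, visits or participants.

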### Sample size and power

The main objective of this trial is to detect weight loss having public health significance. Previous work has indicated that 4-5 pounds of weight loss should reduce systolic blood pressure by ~3 mmHg, which has been estimated to reduce stroke mortality by 6-8%; cardiovascular heart disease mortality by 4-5%; and to reduce risk of incident hypertension by 20% [18,49]. A Monte Carlo simulation study was used to assess the power to detect a clinically meaningful effect on weight loss at months 6 and 18 under a range of conservative assumptions about the effect size, standard deviation, and follow-up with potentially clustered sites [50]. It was assumed that a 4.5 lb difference in weight at 18 months between intervention and control groups would be observed and that the difference at 6 months would be larger. For power calculations, we assumed a standard deviation of change in weight of 12 lbs and that follow-up would be 80% complete. Under these assumptions, for two-sided 0.05-level tests of the null hypothesis, the study should provide approximately 86% power for detecting a difference of 4.5 lbs with SD = 12 lbs. In addition, the study will have the same power to detect the a similar effect size with a smaller sample size if we achieve a higher follow-up rate.

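### The primary model, as most naturally read, gives each arm its own baseline mean weight; a common baseline mean or prespecified baseline-weight adjustment would be slightly more precise at no cost

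*Protocol article*

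**What the plan says.** The Data Analysis section of the protocol article names the outcomes: "The co-primary outcomes are weight loss at 6 and 18 months". The generalized estimating equation models "incorporate baseline, and 6, 12 and 18-month measurements". Later in the section, under missing data, the mean structure is described: the model is to have "parameters for visit specific means for each treatment group". The model is also to "use an unstructured covariance structure".

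Two clauses decide the covariates. The models "will account for study site and other baseline characteristics found not to be balanced by randomization", and they include "baseline covariates associated with study retention". Baseline weight is not named in either clause, and no common baseline mean is stated.

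Randomization and Blinding places random assignment after baseline data collection, stratified by gender and site. Sample size and power assumes a "4.5 lb difference in weight at 18 months between intervention and control groups", and uses the standard deviation of change in weight, 12 lb.

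**The concern.** Baseline weight is measured before assignment, so the two arms have the same true mean at baseline. A model that estimates a separate baseline mean in each arm ignores this. The effect on weight loss is then the month-6 or month-18 arm difference minus the baseline arm difference, which is in essence a difference in change. Unless change is uncorrelated with baseline weight, that contrast has a larger variance than one that uses the equality.

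The second issue is the rule for adjustment. Baseline weight enters as a covariate only if the data show imbalance or a link with retention, so whether the primary estimate is adjusted for it is settled after the data are seen. If baseline weight did enter that way while baseline is also a response, it would stand on both sides of the model.

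At stake are a little precision in both co-primary estimates and a fixed treatment of chance imbalance in the outcome's own baseline value.

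**Working it through.** **Inputs from the article.** 320 participants; two arms with blocks of 2 and 4, so 160 per arm; 80% follow-up, so 0.80 × 160 = 128 per arm; difference 4.5 lb; SD of change 12 lb; two-sided 0.05; stated power about 86%.

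**Assumed.** The article gives no SD of weight, so s = 30 to 60 lb is assumed, equal at baseline and follow-up. The correlation of change with baseline is not given either.

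**1. Reproduce the stated power.** SE = 12 × √(2/128) = 1.50 lb. Power = Φ(4.5/1.50 − 1.96) = Φ(1.04) = 85.1% (84.8% with the t distribution). This agrees with about 86% and uses no baseline adjustment.

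**2. Variance saved.** With equal SDs, 144 = 2s²(1 − ρ), so ρ = 1 − 144/(2s²). The difference in change has variance proportional to 2s²(1 − ρ). With a common baseline mean, or baseline weight as covariate, it is s²(1 − ρ²). The ratio is (1 + ρ)/2. Equivalently, the saving is the squared correlation of change with baseline, which here is −6/s.

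| s (lb) | ρ | variance ratio | SD used (lb) | SE (lb) | power |
|---|---|---|---|---|---|
| difference in change | – | 1 | 12 | 1.500 | 85.1% |
| 30 | 0.920 | 0.960 | 11.76 | 1.470 | 86.5% |
| 45 | 0.964 | 0.982 | 11.89 | 1.487 | 85.7% |
| 60 | 0.980 | 0.990 | 11.94 | 1.492 | 85.4% |

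The gain is 0.3 to 1.4 points of power, worth about 3 to 13 of 320 participants (320 × 0.01 to 320 × 0.04).

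**3. Unequal variances.** If the correlation of change with baseline is r, the saving is r². For r = −0.2 it is 4% (power 86.5%, the same as s = 30 above). For r = −0.3 it is 9% (SD 11.45 lb, power 88.2%). In completers that is 256 × 0.04/0.96 ≈ 11 to 256 × 0.09/0.91 ≈ 25.

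**4. Four-visit check.** A generalized least squares calculation used an unstructured covariance, 160 per arm, 20% with baseline only, and assumed SDs of change between the other visits. The month-18 SEs, free against common baseline mean, were 1.494 and 1.470 lb (s = 30), 1.497 and 1.487 (s = 45), and 1.498 and 1.492 (s = 60). Variance ratios were 0.968, 0.986 and 0.992. The saving is a little smaller than in step 2, because the unstructured covariance already recovers part of it for participants without follow-up.

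**5. Chance imbalance.** At s = 45 lb, the baseline arm difference has SE 45 × √(2/160) = 5.03 lb. Under equal variances the slope of change on baseline is ρ − 1 = −0.036, so a one-SE imbalance moves the change contrast by about 0.18 lb. With r = −0.3 the slope is −0.3 × 12/45 = −0.08 and the shift is about 0.40 lb, 9% of the 4.5 lb target.

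**The case against.** The strongest objection is that the free baseline mean is inferred. The sentence on visit-specific means does not say that baseline is one of those visits, or that its mean is unconstrained. The statement about which measurements enter the model would also fit baseline as a response with a common mean, or as a covariate. A condensed article may leave that parameterisation to a full analysis plan. This stands as a limit on certainty. It does not remove the point, because the article does state a mean structure and the routes by which covariates enter, and neither secures the more precise analysis.

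The imbalance clause could cover baseline weight, so it would be wrong to say that chance imbalance is ignored. What remains is that the clause acts only after the data are inspected.

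The gain is also within the rounding of the stated power in most of the assumed range, and a difference in change already removes nearly all the baseline noise. At s = 45 lb its SE is about 1.5 lb, against 5.07 lb for the raw month-18 difference. Both statements are correct.

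Three stronger readings are tempting and not supported. A reader might infer that the plan is biased; under randomization a difference in change is unbiased. A reader might infer that the trial is underpowered; the power was computed on the SD of change and reproduces without adjustment. A reader might take weight loss in one section and difference in weight in another as a contradiction. The two have the same expectation under randomization, and the sample-size section uses the SD of change, so this is at most a minor looseness.

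**Conclusion.** The point holds as a minor improvement in efficiency and prespecification. On the natural reading of Data Analysis, the co-primary contrasts give up about 1 to 4% of variance, if the weight SD is 30 to 60 lb and equal over time. The saving reaches 9% only if change correlates as strongly as −0.3 with baseline. None of these quantities is in the article. In large samples the alternative is never less precise, randomization makes it valid, and it uses a measurement already collected. No conclusion about the adequacy of the sample size changes.

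**What to change.** State in the analysis plan that the primary model does one of the following, whatever imbalance is observed:

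- keeps baseline weight as a response and constrains its mean to be equal across arms (no arm term at baseline, arm-by-visit terms at 6, 12 and 18 months); or
- takes baseline weight interacting with visit as a covariate, with only the post-baseline visits as responses.

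In either case, name the month-6 and month-18 arm contrasts as the co-primary effects on weight loss, and take baseline weight out of the rules that add covariates for imbalance or retention. This costs about one sentence. It needs no new data and no change to the sample size.
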